**Data Management and Biostatistics Group (CRO):**

Gothia Forum

[name]

[name]

Sweden
**Telefon:** [name]
**Mobil:** [name]

SYNOPSIS OF PROTOCOL: RibaC

(**Riba**virin Loading Dose or Priming and Concentration Targeting for H**C**V Genotype 1)

| TITLE | A Randomized, Open-label, Parallel Group, Multicenter Pilot Study Evaluating the Efficacy and Safety of Alternative Dosing of Ribavirin vs. Standard of Care Dosing in Combination with Peginterferon alpha-2a in Interferon Naïve Patients with Chronic Hepatitis C Genotype 1 Infection | | |
| --- | --- | --- | --- |
| STEERING COMMITTEE | Chairman: [name]  Co-Chairman: [name]  Denmark: [name], [name]  Finland: [name]  Norway: [name]  Sweden: [name], [name] | CLINICAL PHASE | III |
| INDICATION | Chronic hepatitis C (CHC) genotype 1 infection | | |
| OBJECTIVES | Primary   - To demonstrate the efficacy of (A) 2 weeks of high dose of ribavirin (“loading”, ≥26 mg/kg/day for 14 days followed by ≥13 mg/kg/day) followed by concentration targeted (≥ 2.5 mg/L (10.25 μmol/L) 28 days after initiation of ribavirin therapy) dosing of ribavirin vs. (B) 4 weeks of ribavirin dosing before initiation of PEG-interferon dosing (“priming”, ≥13 mg/kg/day) followed by concentration targeted (≥ 2.5 mg/L (10.25 μmol/L) 28 days after initiation of ribavirin therapy) dosing of ribavirin in combination with peginterferon alpha-2a in interferon naïve patients with chronic hepatitis C (CHC) virus genotype 1 infection as compared to (C) standard-of-care dosing of ribavirin (≥13 mg/kg/day without monitoring of ribavirin concentrations) in combination with peginterferon alpha-2a as evaluated by the early viral kinetic response measured by effect on the initial decline of HCV-RNA (during the first days after initiating peginterferon and ribavirin therapy) and second phase decline (day 7 to week 12 of therapy).   Secondary  To prospectively evaluate:   - the efficacy of 2 week loading or 4 week priming followed by concentration targeted dosing of ribavirin in combination with peginterferon alpha-2a in interferon naïve patients with chronic hepatitis C (CHC) virus genotype 1 infection as compared to standard-of-care dosing of ribavirin in combination with peginterferon alpha-2a as evaluated by the proportion of patients achieving VRVR ( “very rapid virologic response” i.e. HCV-RNA below 1000 U/mL at treatment day 7 after intiation of PEG-interferon), RVR (“rapid virologic response”, undetectable HCV-RNA at treatment day 28 after intiation of PEG-interferon), cEVR (“complete early virologic response”, i.e. undetectable HCV-RNA at treatment week 12 after intiation of PEG-interferon), and pEVR (“partial early virologic response”, i.e. decline of HCV-RNA by at least 2 log10 compared with baseline at treatment week 12 after intiation of PEG-interferon). - the efficacy of 2 week loading or 4 week priming followed by concentration targeted dosing of ribavirin in combination with peginterferon alpha-2a in interferon naïve patients with chronic hepatitis C (CHC) virus genotype 1 infection is superior to standard-of-care dosing of ribavirin, peginterferon alpha-2a therapy as evaluated by sustained virological response (SVR, undetectable HCV-RNA 24 weeks after end of treatment). - the predictive value of monitoring of viral load at day 0 (before the 1st dose of peginterferon alpha-2a), day 3, day 7 (before the 2nd dose of peginterferon alpha-2a), and day 28 (before the 5th dose of peginterferon alpha-2a) determining which patients will obtain a sustained virological response (SVR) when treated with ribavirin and peginterferon alpha-2a therapy. - the association between the trough concentrations of ribavirin (day 1, day 3, day 7, day 14, day 28, week 8, week 12, week 18, and end-of-treatment), and the therapeutic efficacy of ribavirin and peginterferon alpha-2a therapy. - The association between plasma IP-10 (days 0, 1, 3, 7, and 14, and weeks 8, 18, and 24), and the therapeutic efficacy of ribavirin and peginterferon alpha-2a therapy. - the effect of IL-28B ploymorfism on the viral kinetic response. - the effect of baseline vitamin D concentrations on the viral kinetic response. - the effect of baseline IP-10 concentrations on the viral kinetic response. - the association between liver histology as evaluated by the Ishak scoring system (modified HAI score) and steatosis grading if a liver biopsy has been performed, and the therapeutic efficacy of peginterferon alfa-2 combination therapy with ribavirin. - the association between liver stiffness as evaluated by the FibroScan if this has been performed and the therapeutic efficacy of peginterferon alfa-2 combination therapy with ribavirin. - the association between liver fibrosis as evaluated by the GUCI and APRI indexes as well as hyaluronic acid, and the therapeutic efficacy of peginterferon alfa-2 combination therapy with ribavirin. - the association between body mass index (BMI), waist circumference, weight and age, and the therapeutic efficacy of peginterferon alfa-2 combination therapy with ribavirin. - the predictive value of monitoring CD56 negative NK, CD4+ CD38+, CD8+ CD38+, CD8+CD16+, Foxp3+, and pDC (CD303+) cells in peripheral blood and liver biopsies as analyzed by FACS prior to and after the initiation of therapy for determining which patients will obtain a sustained virological response (SVR) when treated with peginterferon alfa-2 and ribavirin combination therapy. - the predictive value of quantifying mRNA expression in pre-treatment liver biopsies for IFI-27, IP-10, CXXL-6, IL-2, IL-8, IL-10, -IFN, TNF-, KRT19, COL1A1, MMP7, TIMP1, FASL, AIF1 for determining which patients will obtain a sustained virological response (SVR) when treated with peginterferon alfa-2 and ribavirin combination therapy.   Others:  To prospectively evaluate:   - the predictive value of monitoring the trough concentrations of ribavirin (day 1, day 3, day 7), and the final steady-state concentration of ribavirin.. - the safety of peginterferon alpha-2a combination therapy with concentration targeted dosing of ribavirin in combination peginterferon alpha-2a, based on accumulated number of adverse events and severe adverse events as well as the impact on quality of life during treatment and follow-up phase. - the safety of peginterferon alpha-2a combination therapy with concentration targeted dosing of ribavirin in combination peginterferon alpha-2a, with particular regards to the number of patients in each treatment arm developing anemia grade 1 (10.5-9.5 g/dL), grade 2 (9.4-8.0 g/dL), grade 3 (7.9-6.5 g/dL), and grade 4 (<6.5 g/dL). | | |
| TRIAL DESIGN | Multicenter, randomized, open-label, parallel group pilot study.  Randomization to the three treatment arms A, B and C will be stratified by gender, age above or below 40 years, and presence of liver cirrhosis/non-cirrhosis (as evaluated by the Gothenburg University Cirrhosis Index (GUCI) 1.0). | | |
| DISCONTINUATION SCHEME | Treatment will be stopped in patients having a decline of HCV-RNA less than 2-log10 after 12 weeks or detectable HCV-RNA after 24 weeks of study treatment as measured by Roche COBAS AmpliPrep/COBAS TaqMan HCV Test (≤15 IU/mL) | | |
| NUMBER OF SUBJECTS | Total of 105 patients, 35 per treatment group. | | |
| TARGET POPULATION | Men and women >18 years old with CHC genotype 1 will be enrolled in this study. Patients must have quantifiable HCV-RNA, and must have compensated liver disease (Child-Pugh Grade A). Liver biopsies and/or FibroScan evaluations are encouraged especially for patients with a Gothenburg University Cirrhosis Index (GUCI, a cirrhosis index calculated by (normalized AST x PK-INR x 100) / Platelet count (x 109/L)) 1.0, but not mandatory. Patients with other forms of liver disease, human immunodeficiency virus (HIV) infection, hepatocellular carcinoma, anemia, pre-existing severe depression or other psychiatric disease, significant cardiac disease, renal disease, seizure disorders, or severe retinopathy, or previously treated with interferon/ peg-interferon with or without ribavirin are excluded. | | |
| SELECTION CRITERIA | Inclusion Criteria:   - Written informed consent - Male and female patients 18 years of age - Serologic evidence of chronic hepatitis C infection by an anti-HCV antibody test - Serum HCV-RNA 15 IU/mL. - HCV genotype 1 infection confirmed within the past 2 years preceding the initiation of test drug dosing. - Compensated liver disease (Child-Pugh Grade A clinical classification) - Patients with cirrhosis or transition to cirrhosis must have an abdominal ultrasound, CT scan, or MRI scan without evidence of hepatocellular carcinoma and a serum AFP ≤100 ng/mL within 2 months of randomization - Negative urine or blood pregnancy test (for women of childbearing potential) documented within the 24-hour period prior to the first dose of study drug - All fertile males and females receiving ribavirin must be using effective contraception during treatment and during 4 months for female patients / 7 months for male patients after end of treatment - Subject must weigh between 45 and 105 kg at screening   Exclusion Criteria:   - Women with ongoing pregnancy or breast feeding - IFN/ peg-interferon with or without ribavirin therapy at any previous time - Therapy with any systemic anti-viral, anti-neoplastic or immunomodulatory treatment (including supraphysiologic doses of steroids and radiation) £6 months prior to the first dose of study drug - Any investigational drug 6 weeks prior to the first dose of study drug. - HCV genotype 2, 3, 4, 5, 6, or 7 infection. - Positive test at screening for anti-HAV IgM Ab, HBsAg, anti-HBc IgM Ab, anti-HIV Ab - Evidence of a medical condition associated with chronic liver disease other than HCV (e.g., hemochromatosis, autoimmune hepatitis, metabolic liver disease, alcoholic liver disease, toxin exposures) - History or other evidence of decompensated liver disease - Neutrophil count <1500 cells/mm3 or platelet count <90,000 cells/mm3 at screening - Serum creatinine level >2 mg/dl (>124 µmol/L) or creatinine clearance ≤50 ml/minute at screening - Severe psychiatric disease, especially depression, as judged by the treating physician. - History of a severe seizure disorder or current anticonvulsant use - History of immunologically mediated disease, severe chronic pulmonary disease associated with functional limitation, severe cardiac disease, major organ transplantation or other evidence of severe illness, malignancy, or any other conditions which would make the patient, in the opinion of the investigator, unsuitable for the study - Thyroid dysfunction not adequately controlled (TSH and T4 levels out of normal range) - Evidence of severe retinopathy (e.g. CMV retinitis, macula degeneration) or clinically relevant ophthalmological disorder due to diabetes mellitus or hypertension - Evidence of drug abuse (including excessive alcohol consumption) in accordance with local therapeutic traditions. - Inability or unwillingness to provide informed consent or abide by the requirements of the study - Male partners of women who are pregnant - emoglobin <12 g/dL in women or <13 g/dL in men at screening. - Any patient with an increased baseline risk for anemia (e.g. thalassemia major, spherocytosis, history of GI bleeding, etc) or for whom anemia would be medically problematic coagulopathia. - Patients with documented or presumed coronary artery disease or cerebrovascular disease should not be enrolled if, in the judgment of the investigator, an acute decrease in hemoglobin by up to 4 g/dL (as may be seen with ribavirin therapy) would not be well-tolerated - Evidence of allergy to PEG-IFN or ribavirin. | | |
| LENGTH OF STUDY | Period of enrollment: 52 weeks | | |
| Group A (“Loading”): PEG-IFN α-2a 180 g/week plus loading (≥26 mg/kg/day for 2 weeks followed by ≥13 mg/kg/day) and concentration targeted (≥ 2.5 mg/L, i.e ≥ 10.25 mol/L, as measured after 4 weeks of therapy) dosing of ribavirin and response guided treatment duration (RVR 24 weeks, non-RVR 48 weeks, pEVR consider 72 weeks), follow-up period 24 weeks | | |
| Group B (“Priming”): Standard-of-care dosing of ribavirin (≥13 mg/kg/day) without PEG-IFN for 4 weeks followed by 24-48 additional weeks of PEG-IFN α-2a 180 g/week plus standard-of-care dosing of ribavirin (≥13 mg/kg/day) and concentration targeted (≥ 2.5 mg/L, i.e ≥ 10.25 mol/L, as measured after 28 days after the initiation of ribavirin) dosing of ribavirin and response guided treatment duration (RVR 28 weeks, non-RVR 52 weeks, pEVR consider 76 weeks), follow-up period 24 weeks  Group C (“Standard-of-Care”): PEG-IFN α-2a 180 g/week plus standard-of-care dosing of ribavirin (≥13 mg/kg/day without any measurement of ribavirin concentration) and response guided treatment duration (RVR 24 weeks, non-RVR 48 weeks, pEVR consider 72 weeks), follow-up period 24 weeks | | |
| DURATION OF STUDY | October 2010 till July 2013 including a recruitment period of 52 weeks, with an interim analysis of the primary study endpoints after all patients reached treatment 12 week. | | |
| INVESTIGATIONAL PRODUCT(S) DOSE/ ROUTE/ REGIMEN | Peginterferon α-2a  Copegus (ribavirin): 200-400 mg/tablet | | |
| ASSESSMENTS OF: |  | | |
| - EFFICACY | Primary Variable:   - The early virological response as measured by decline in HCV-RNA during the first 12 weeks of peginterferon alpha-2a and ribavirin therapy in the three study arms.   Secondary Variables:   - VRVR, RVR, cEVR, and pEVR rates defined as percentage of patients achieving these goals as measured by TaqMan PCR in the three study arms. - Percentage of patients with non-detectable HCV-RNA at study day 1, 3, 7, 14, 21, 28, week 8, week 12, end of treatment, and 24 weeks after completion of treatment as measured by TaqMan PCR as compared to day 0. - SVR rate defined as percentage of patients with non-detectable HCV-RNA as measured by TaqMan PCR at 24 weeks post completion of the treatment period in the three study arms. - Relapse rates defined as percentage of patients with non-detectable HCV-RNA as measured by TaqMan PCR at the end-of-treatment but with detectable HCV-RNA 24 weeks post completion of the treatment period in the three study arms. - SVR rate and percentage of patients with normal serum ALT levels at 24 weeks after completion of the treatment period in the total patient population, and its association with the following factors: - early virological response - pharmacokinetic response to ribavirin | | |
| - SAFETY | - Adverse event rate and profile - Laboratory assessments - An independent DSMB will evaluate safety after the first 30 patients have reached treatment weeks 2 and 12. - The use of erythropoietin (NeoRecormon) ≥3000 IE 3 times week sc initially in the event of anemia is permitted throughout the study at the discretion of the treating physician with the exception if the patient has any of the following exclusion criteria for the use of erythropoietin: platelet count >500,000, risk of thrombosis, or poorly controlled hypertension, especially if hemoglobin decreases persistently to < 10.0 g/dL or in the event of a rapid decrease in hemoglobin exceeding 4.0 g/dL over a 2 week period. If erythropoietin is initiated, a new ribavirin concentration at local lab should be evaluated after 4 weeks in Groups A (“Loading”) and B (“Priming”). - In the event of anemia, dose reductions of ribavirin are permitted in all study arms throughout the study at the discretion of the treating physician. - If hemoglobin decreases to < 8.0 g/dL, ribavirin should be discontinued. - If hemoglobin decreases to < 7.0 g/dL, blood transfusion should be considered at the discretion of the treating physician. - If hemoglobin decreases to < 6.5 g/dL, blood transfusion should be given. - Patients will discontinue therapy if the decrease in plasma HCV RNA between week 12 and baseline is ≤ 2 log10 IU/mL or if plasma HCV RNA is still detectable by treatment week 24. - The use of granulocyte growth factors are permitted throughout the study in accordance with local or national treatment guidelines at the discretion of the treating physician. - The members of the Steering Committee in each respective country will be responsible for monitoring the participating centers in their country. One or more experienced monitor is recommended per participating country. - Only experienced treatment centers willing to include ≥ 5 patients will be permitted to participate in the study. - All serious adverse events in the study will be reported to IST and Welwyn. | | |
| - QUALITY OF LIFE | - SF 36 | | |
| STATISTICAL ANALYSES | Sample Size Calculation: This is a pilot trial with the viral kinetic response measured as described above, during the first 12 weeks of therapy as primary endpoint with the aim of investigating the feasibility and safety of “loading” and “priming” dosing of ribavirin in conjunction with PEG-IFN for chronic HCV genotyp 1. To demonstrate an increase in the reduction of HCV RNA from day 0 to 3 from 0.9 log10 IU/mL in Group C (Standard-of-Care) to 1.4 log10 IU/mL in Group A or B or an increase in the reduction of HCV RNA from day 7 to 28 from 0.4 log10 IU/mL/week in Group C (Standard-of-Care) to 0.6 log10 IU/mL/week in Group A or B the study requires at least 35 patients per study arm. The statistical power (chance) for the study to detect a superior effect in Group A or B as compared to C is 80%. Statistical sample-size calculation is based on z-test for differences between proportions and is one-sided with a significance level of 5%.  Analysis Plan: Intention-to-treat and Per-protocol analysis on primary endpoints will be performed for patients receiving at least one dose of the study drugs. Additionally, an analysis of SVR with regards to whether or not the target concentration of ribavirin 2.5 mg/L (10.25 μmol/L) at day 28 was achieved across all study arms will be performed. | | |

TABLE OF CONTENTS..................................................................................................Page

Part I: Study design and conduct [1](#__RefHeading___Toc138151525)

1. background and rationale [1](#__RefHeading___Toc138151526)

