## Secondary Objectives

To prospectively evaluate:

- the efficacy of 2 week loading or 4 week priming followed by concentration targeted dosing of ribavirin in combination with peginterferon alpha-2a in interferon naïve patients with chronic hepatitis C (CHC) virus genotype 1 infection as compared to standard-of-care dosing of ribavirin in combination with peginterferon alpha-2a as evaluated by the proportion of patients achieving VRVR ( “very rapid virologic response” i.e. HCV-RNA below 1000 U/mL at treatment day 7 after intiation of PEG-interferon), RVR (“rapid virologic response”, undetectable HCV-RNA at treatment day 28 after intiation of PEG-interferon), cEVR (“complete early virologic response”, i.e. undetectable HCV-RNA at treatment week 12 after intiation of PEG-interferon), and pEVR (“partial early virologic response”, i.e. decline of HCV-RNA by at least 2 log10 compared with baseline at treatment week 12 after intiation of PEG-interferon).
- the efficacy of 2 week loading or 4 week priming followed by concentration targeted dosing of ribavirin in combination with peginterferon alpha-2a in interferon naïve patients with chronic hepatitis C (CHC) virus genotype 1 infection is superior to standard-of-care dosing of ribavirin, peginterferon alpha-2a therapy as evaluated by sustained virological response (SVR, undetectable HCV-RNA 24 weeks after end of treatment).
- the predictive value of monitoring of viral load at day 0 (before the 1st dose of peginterferon alpha-2a), day 3, day 7 (before the 2nd dose of peginterferon alpha-2a), and day 28 (before the 5th dose of peginterferon alpha-2a) for determining which patients will obtain a sustained virological response (SVR) when treated with ribavirin and peginterferon alpha-2a therapy.
- the association between the trough concentrations of ribavirin (day 1, day 3, day 7, day 28, week 8, week 12, week 16, and end-of-treatment), and the therapeutic efficacy of ribavirin and peginterferon alpha-2a therapy.
- The association between plasma IP-10 (days 0, 1, 3, 7, and 14, and weeks 8, 18, and 24), and the therapeutic efficacy of ribavirin and peginterferon alpha-2a therapy.
- the effect of IL-28B polymorfism on the viral kinetic response and SVR.
- the effect of baseline vitamin D concentrations on the viral kinetic response and SVR.

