## Study Assessments

### Efficacy Assessments

Efficacy assessments consist of serum HCV-RNA via PCR and ALT determination.

Quantitative viral titers (COBAS TaqMan 48™)) will be obtained during screening, day 28, week 12, week 24, End-of-Treatment, and 24 weeks post-end of treatment and sent to local lab for assessment.

Patients who discontinue from treatment prematurely, are expected to return for sampling for HCV RNA at end-of-treatment, and 24 weeks post-end of treatment.

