- In the event of anemia, dose reductions of ribavirin are permitted in all study arms throughout the study at the discretion of the treating physician.
- If hemoglobin decreases to < 8.0 g/dL, ribavirin should be discontinued.
- If hemoglobin decreases to < 7.0 g/dL, blood transfusion should be considered at the discretion of the treating physician.
- If hemoglobin decreases to < 6.5 g/dL, blood transfusion should be given.
- Patients will discontinue therapy if the decrease in plasma HCV RNA between week 12 and baseline is ≤ 2 log10 IU/mL or if plasma HCV RNA is still detectable by treatment week 24.
- The members of the Steering Committee in each respective country will be responsible for monitoring the participating centers in their country. One or more experienced monitor is recommended per participating country.
- Only experienced treatment centers willing to include ≥ 5 patients will be permitted to participate in the study.
- All serious adverse events in the study will be reported to IST and Welwyn.

Patients will also be assessed for safety after their last dose of test medication following premature discontinuation from the study. This includes a laboratory evaluation at least 12 weeks following the final dose of test drug (for details please refer to section 3.1). Generally patients should be encouraged to stay in the trial. Counseling about contraception and behaviors associated with an increased risk of pregnancy must be repeated on a monthly basis.

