## Treatment Duration

Regardless of treatment arm, all patients with undetectable HCV RNA at week 4 (RVR) as analyzed by the local lab will receive 24 weeks of combination therapy. Similarly patients not achieving RVR will receive 48 weeks of therapy with the exception of patients having detectable HCV RNA at week 12 but not at week 24 (pEVR) where treatment for 72 weeks may be considered if the patient is willing to extend therapy beyond 48 weeks.

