## Stopping Rule

Regardless of treatment arm, all patients achieving ≤ 2 log10 reduction in HCV RNA by week 12 or having detectable HCV RNA at week 24, will discontinue therapy and be considered as “non-responders” not having achieved SVR.

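### The virological stopping rule is inconsistent on its time origin in Group B, its reference HCV-RNA sample and its 2 log10 boundary

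*Protocol*

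**What the plan says.** The rule appears in four places in the protocol.

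- Synopsis, Discontinuation Scheme: stop for a "decline of HCV-RNA less than 2-log10 after 12 weeks or detectable HCV-RNA after 24 weeks of study treatment".
- Section 5.3.2 (Safety Assessments), with the same rule in the synopsis safety row: "Patients will discontinue therapy if the decrease in plasma HCV RNA between week 12 and baseline is ≤ 2 log10 IU/mL". HCV RNA still detectable at week 24 is the other ground.
- Section 7.5 (Stopping Rule) says that, in every arm, "all patients achieving ≤ 2 log10 reduction in HCV RNA by week 12 or having detectable HCV RNA at week 24" stop therapy and count as non-responders without SVR.

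The matching response category, pEVR, is defined in section 2.2 as a "decline of HCV-RNA by at least 2 log10 compared with baseline at treatment week 12 after intiation of PEG-interferon".

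For the measurements, section 5.3.1 says that quantitative titres "will be obtained during screening, day 28, week 12, week 24, End-of-Treatment, and 24 weeks post-end of treatment and sent to local lab for assessment". The central laboratory list (section 5.3.1, Viral Kinetic) adds days 0, 3 and 7, and day -28 for Group B. Appendix 5 has the central virology samples shipped when the study is complete. Section 5.1 places baseline on the first day of drug, before PEGASYS and Copegus.

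**The concern.** Group B takes ribavirin alone for four weeks before PEG-IFN, so any rule stated in treatment weeks needs a named start for that arm. None of the four statements gives one. This is an open-label, multicentre trial in which sites apply the rule themselves, and section 7.5 turns a stop into a failure for SVR. If sites read the clock differently, only Group B is affected, and the B versus C comparison of SVR would carry part of that difference.

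The reference sample and the boundary raise a second problem. A site that has only the screening value may stop a patient for inadequate decline whom the day 0 sample later classifies as pEVR. At exactly 2 log10 the protocol's own definitions make the same patient both a responder and a stop.

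**Working it through.** **1. Time origin, sections side by side**

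Counting from the first ribavirin dose:
- Synopsis and section 3.1 give Group B durations of 28/52/76 weeks. Groups A and C have 24/48/72, and 24 + 4 = 28, 48 + 4 = 52, 72 + 4 = 76. The stated figures are reproduced exactly, so priming is counted as treatment there.
- Appendix 5 calls day 0 the day of the first study-medication dose.

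Counting from PEG-IFN:
- pEVR (section 2.2) counts week 12 from PEG-IFN.
- Section 5.3.1 gives Group B's priming days negative numbers (-28, -27, -21).
- Section 7.5 (Treatment Duration) covers "Regardless of treatment arm, all patients with undetectable HCV RNA at week 4 (RVR) as analyzed by the local lab" and gives them 24 weeks of combination therapy, which excludes priming.
- Section 1.4.4.2 places a 48-week treatment period after priming.
- Appendix 5, in the same sentence as the gloss above, puts day 0 just before the first PEG-IFN dose. In Group B the two definitions are 28 days apart.

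On the ribavirin clock, Group B's checks fall at PEG-IFN weeks 12 - 4 = 8 and 24 - 4 = 20. On the PEG-IFN clock they fall at 12 and 24 in every arm.

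**2. Reference sample**

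Screening may be up to 56 days before first drug (section 5.2): 56/7 = 8 weeks before PEG-IFN in A and C, and 8 + 4 = 12 weeks in B. No section names screening as the rule's baseline.

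**3. Inequality at a decline of exactly 2 log10**

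| Source | Result |
| --- | --- |
| Synopsis, Discontinuation Scheme (< 2) | continue |
| Synopsis safety row, 5.3.2, 7.5 (≤ 2) | stop |
| pEVR (≥ 2) | response |

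**4. Illustrative size if the ribavirin clock were used**

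Inputs from section 9.3: first-phase decline f = 0.9 log10 (C) or 1.4 (A/B); second-phase slope 0.4 or 0.6 log10/week. The 15 IU/mL limit is from the synopsis. Assumptions: baseline 6 log10; slopes normal with SD 0.2 to 0.3; the slope holds beyond day 28. Decline at PEG-IFN week w = f + slope × (w - 1).

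- Four fewer PEG-IFN weeks cost 4 × 0.4 = 1.6 to 4 × 0.6 = 2.4 log10 on average. Mean decline at week 8 is still 0.9 + 0.4 × 7 = 3.7 to 1.4 + 0.6 × 7 = 5.6, so only slow responders are affected.
- The decline needed to become undetectable is 6 - log10(15) = 4.82.
- Group C kinetics: slope needed is (4.82 - 0.9)/19 = 0.206 at week 20 and (4.82 - 0.9)/23 = 0.170 at week 24. The share between them is 4.1% (SD 0.2) or 3.7% (SD 0.3), that is 1.4 or 1.3 of 35.
- A/B kinetics: (4.82 - 1.4)/19 = 0.180 and (4.82 - 1.4)/23 = 0.149. The share is 0.6% (SD 0.2) to 1.5% (SD 0.3), that is 0.2 to 0.5 of 35.
- 2 log10 check, Group C kinetics: slope needed is (2 - 0.9)/7 = 0.157 at week 8 and (2 - 0.9)/11 = 0.100 at week 12, a further 4.5 to 5.0% of patients. All have slopes below 0.170, so they are still detectable at PEG-IFN week 24 and are non-responders on either clock. They are stopped earlier but not reclassified.

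**5. Illustrative effect of the reference sample**

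Assume the screening-to-day-0 difference has SD 0.2 to 0.4 log10. A patient 2.2 log10 down from day 0 reads 2 log10 or less from screening with probability Φ(-0.2/0.2) = 0.16 to Φ(-0.2/0.4) = 0.31. With f = 0.9, that patient's slope is (2.2 - 0.9)/11 = 0.118, which gives 0.9 + 0.118 × 23 = 3.6 log10 by week 24, short of 4.82. In this model the choice of reference changes when the patient stops and whether the stop agrees with pEVR, but not SVR status.

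**The case against.** The strongest reply is that the protocol in practice runs on a PEG-IFN clock. Study days are numbered that way, day 28 precedes the fifth PEG-IFN dose, and the stopping rule in section 7.5 directly follows a paragraph that uses the same week labels for RVR and pEVR. No HCV-RNA sample is scheduled at PEG-IFN week 8 or 20, so an earlier check in Group B would have nothing to use. This stands. It makes the PEG-IFN reading the more likely one, but it does not remove the synopsis wording, the durations that count priming or the double definition of day 0.

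A reader might infer that Group B is in fact stopped four weeks early and that SVR is therefore biased against it. The documents do not establish that. A reader might also infer that the missing local baseline puts the arms on different clocks. It does not: the gap exists in all arms, and only the longest possible interval from screening to PEG-IFN differs. Nor can the two shares in the working be added to about 8 to 9% (3 of 35), because the first group fails on either clock.

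The visit tables of section 5.1 were not in the text available for checking. They might define the weeks by arm or list a local baseline sample. The boundary conflict touches only declines of exactly 2 log10 and is minor.

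**Conclusion.** The rule is wrong as written, in a limited sense. It contradicts itself on the inequality. It leaves its time origin in Group B open while other sections count both ways. It also relies on a baseline that the listed local samples do not supply when the decision falls due. The numerical consequence is small and conditional: about 4% of Group B (1 to 2 of 35) reclassified for SVR under Group C kinetics, or 0.6 to 1.5% under the protocol's A/B values, and only if the ribavirin clock were used. Those figures rest on the assumed 6 log10 baseline, the assumed slope SDs and a slope extended past day 28. The contradictions themselves rest on no assumption beyond the unavailable section 5.1 tables. The point is worth settling because the rule decides who counts as a non-responder and the correction costs almost nothing.

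**What to change.** Reconcile the synopsis (discontinuation scheme, Group B durations and safety row), sections 2.2, 3.1, 5.1, 5.3.1 and 5.3.2, both sections numbered 7.5, and Appendix 5, so that the rule states:

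- one time origin, written out for every arm as weeks since a named first dose;
- one inequality that does not overlap with the pEVR definition;
- one named reference HCV-RNA sample whose result is available when the decision is made.

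Report pEVR and non-response on that same clock and reference. Which clock, threshold and sample to use is for the steering committee. The cost is protocol wording. If the committee names a sample not now measured locally, add one local HCV-RNA run per patient, which could use blood already drawn.
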